#### Strategies to improve adherence to interventions

The investigators will inform the patients of the benefits and precautions of AVS surgery and thus build and maintain trust with patients.

#### Relevant concomitant care

To maintain the accuracy of AVS outcome, MRAs such as spironolactone were not permitted to be taken since 4 weeks before AVS. After AVS, for those who choose to be treated with medication, they will be instructed to take MRAs first, and if blood pressure is poorly controlled (SBP > 140 mmHg or DBP > 90 mmHg), they will be recommended to take MRAs combined with other antihypertensive drugs (ACEi/ARB or CCB will be firstly considered).

#### Provision for post-trial care

This trial’s target is to assess the effect of preoperative supine time for diagnostic efficiency of AVS. There is no anticipated compensation for trial participation.

### Outcomes

#### Basic information

Before treatment, researchers will collect basic characteristics (such as gender, age, education, marital status, height, and weight) and medical history (such as blood pressure, type and dose of antihypertensive drugs, serum potassium, orthostatic ARR) of recruited participants.

#### Primary outcome

Rate of biochemical remission

Biochemical outcome evaluation in 3 and 6 months after AVS: serum potassium, orthostatic ARR. All these data will be recorded in the PASO table [11] (feasible criteria for the classification of outcomes of adrenalectomy for the treatment of unilateral primary aldosteronism). The detailed criteria of complete, partial, and absent biochemical remission are shown in Fig. 3.

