## Introduction

### Background

Primary aldosteronism (P.A.) is a disease caused by excessive autonomous aldosterone from adrenal tumor or hyperplasia, characterized by the inhibition of the renin-angiotensin system, sodium retention, and excessive excretion of potassium and hydrogen [1]. P.A. was regarded as a rare disease since it was first discovered by Conn in 1955 [2] for it was found only in less than 1% of hypertensive patients [3]. However, recent studies have noticed that P.A. accounts for 5% of hypertensive patients in primary care [4], and the prevalence in patients with resistant hypertension has reached 17–23% [5]. A study on the Chinese population with newly detected hypertension also profiled at least 4% of patients suffered P.A [6]. Besides, P.A. is a significant cause of increased stroke risk, coronary artery disease, atrial fibrillation, ventricular hypertrophy, and renal damage [7]. It could be assumed that most P.A. patients missed proper diagnosis and suffered cardiovascular damage, which may explain the limitation of traditional hypertensive drugs on resistant hypertension.

P.A. includes two main subtypes: aldosterone-producing adenoma (APA, accounting for about 35%) and bilateral adrenal hyperplasia (BAH, accounting for about 60%). Other rare subtypes include primary adrenal hyperplasia, family aldosteronism, and aldosterone-secreting adrenocortical carcinoma [1, 8]. It is controversial whether P.A. patients should be treated with surgery or drugs [9]. Unilateral adrenalectomy is suggested for most patients with adenoma or primary adrenal hyperplasia, which statistically satisfied the goal of clinical and laboratory remission [10, 11]. However, anti-RAAS drugs and glucocorticoids are more recommended for BAH or family aldosteronism patients [12].

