#### Participant enrollment and preoperative preparation

Patients will be initially included or excluded during hospitalization in the endocrinology department based on the patient’s basic information and medical history. The selected patients will be randomly divided into the 15-min supine group (experimental group) or the 2-h group (control group). Before surgery, patients will be informed of the risks, possible complications and expected examination results of AVS surgery, and signed informed consent.

Preoperative examination includes the following: (1) Adrenal enhanced CT: routine CT examination is performed to evaluate whether there are nodules, hyperplasia, and anatomical variation in bilateral adrenal glands; MRI examination was the alternative option for patients with renal insufficiency. (2) Necessary examination for surgery: complete blood count, serum chemistry profile, routine urinalysis, coagulation function, blood group, epidemic disease profile, electrocardiogram; (3) serum potassium, renin, and aldosterone.

Preoperative preparation includes the following: (1) replacing the drugs that may affect the serum renin and aldosterone, especially the mineralocorticoid receptor antagonist (MRAs); (2) keeping serum potassium in the normal range if possible (at least ≥ 3.0 mmol/l); (3) keeping blood pressure within the range of 140/100mmHg.

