#### Postoperative management and follow-up

The result of AVS will be interpreted by an experienced doctor. Briefly, in this study, S.I. ≥ 2 indicates successful AVS, and L.I. ≥ 2 indicates unilateral primary aldosteronism. Unilateral P.A. patients will be suggested to accept the unilateral adrenalectomy, and bilateral adrenal hyperplasia patients will be recommended for medication therapy.

Patients will be followed up after unilateral adrenalectomy or optimized anti-hypertensive medicine therapy at 3 months and 6 months with clinical examination. All these data would be recorded in the PASO table, including the blood pressure, type, and dose of antihypertensive drugs, serum potassium, and orthostatic ARR.

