### Statistical analysis

An independent statistician will complete the statistical analysis of the study result via the SPSS V25.0. Baseline characteristics will be described by descriptive statistics. *x̅* ± *s* will represent continuous variables with the normal distribution, and the *t* test will compare the differences between the two groups. The Mann–Whitney *U* test will be used in continuous variables that were not normally distributed. Categorical variables will be expressed as frequency (%), and the chi-square test will be used to compare the differences between the two groups. Effect estimates will be provided with corresponding 95% confidence intervals, and *P* values ≤ 0.05 will be considered statistically significant. All randomized participants will be included in the analyses, and data will be analyzed in the group where the participants were randomized initially. The experimental group includes the available data from the 15-min supine group, and the control group includes the available data from the 2-h supine group. The principles of intention-to-treat analysis will be used to preserve the unique benefit of randomization, regardless of whether that participant received the allocated intervention. Multiple imputation (MI) using the mice package in R will be applied to analyze the missing data.

Further secondary analyses will include pre-specified subgroup analyses according to age and the two stratification/minimization variables, investigated by introducing the relevant interaction with treatment allocation into the regression model. In addition, to assess the stability of any intervention effect, we will fit a mixed model for the primary outcome at 3 and 6 months, adjusted for baseline measures.

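### The primary remission rate applies adrenalectomy criteria to operated and medicated patients alike, so equal pooled rates would not by themselves show that subtyping is unaffected

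*Protocol article*

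**What the plan says.** The section Primary outcome defines the endpoint by "Biochemical outcome evaluation in 3 and 6 months after AVS: serum potassium, orthostatic ARR", classified as complete, partial or absent remission in the PASO table. It describes that table as "feasible criteria for the classification of outcomes of adrenalectomy for the treatment of unilateral primary aldosteronism".

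Postoperative management and follow-up covers both treatment routes: "Patients will be followed up after unilateral adrenalectomy or optimized anti-hypertensive medicine therapy at 3 months and 6 months". It then adds "All these data would be recorded in the PASO table". Unilateral disease (L.I. ≥ 2) leads to a suggestion of adrenalectomy, and bilateral hyperplasia to a recommendation of medication.

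On drug treatment, Relevant concomitant care says "for those who choose to be treated with medication, they will be instructed to take MRAs first", with other antihypertensives added if blood pressure is poorly controlled. Before AVS, the preparation includes "replacing the drugs that may affect the serum renin and aldosterone, especially the mineralocorticoid receptor antagonist (MRAs"), and MRAs are barred for 4 weeks to protect the accuracy of the result.

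The Statistical analysis section says "All randomized participants will be included in the analyses". Trial design gives the hypothesis: a shorter supine time does not affect the subtyping efficacy of AVS.

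**The concern.** The criteria are described as made for one situation (unilateral disease, after adrenalectomy) and are used in two. In operated patients, potassium and orthostatic ARR reflect whether the source of excess aldosterone was removed. In medicated patients, the same two quantities may be read on drugs that the article itself regards as able to disturb renin and aldosterone. One pooled remission rate then mixes two different quantities.

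This matters because of what the trial asks. Supine time can affect 3- and 6-month outcomes mainly by changing the AVS classification and so the treatment route. If a unilateral patient is misread as bilateral and receives an MRA, potassium and ARR may still meet the remission criteria. That patient's error then leaves no trace in the primary endpoint. The hypothesis is one of no effect, so dilution of this kind pushes towards the conclusion the trial expects.

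**Working it through.** **Is the premise in the text?** Set side by side, the sections agree. The criteria are for adrenalectomy (Primary outcome). Both treatment routes are recorded in the same table (Postoperative management and follow-up). All randomised patients are analysed (Statistical analysis). Medicated patients start with MRAs (Relevant concomitant care). MRAs may affect renin and aldosterone (Participant enrollment and preoperative preparation). No separate criterion for medicated patients appears in the text shown.

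**Is there a plan figure to reproduce?** No. The Sample size section gives an effect size of 0.5 and 60 per group, but no remission rate on either route. The size below therefore rests on assumptions.

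**Inputs**
- Unilateral share u = 0.35: the Background figure for aldosterone-producing adenoma in P.A. generally, not for this trial's patients.
- Additional unilateral patients missed in one arm: 0.20 (assumed).
- Remission after correct surgery: 0.95 (assumed).
- Share of missed patients scored as remission on MRAs: m = 0.30 to 0.70 (assumed).

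**Pooled endpoint.** Difference between arms = u × 0.20 × (0.95 − m) = 0.07 × (0.95 − m).
- m = 0.30: 0.07 × 0.65 = 4.55 points
- m = 0.50: 0.07 × 0.45 = 3.15 points
- m = 0.70: 0.07 × 0.25 = 1.75 points

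**Without dilution.** If no missed patient scored as remission (m = 0), the difference would be 0.07 × 0.95 = 6.65 points. Counting only PASO success after adrenalectomy, over all randomised, gives the same value: 33.25% against 26.6%.

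**Other unilateral shares.** With u = 0.50 the pooled difference is 0.10 × (0.95 − m) = 2.5 to 6.5 points, against 9.5 undiluted. With u = 0.65 it is 0.13 × (0.95 − m) = 3.25 to 8.45, against 12.35.

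**Precision at 60 per arm.** The largest 95% half-width for a difference in proportions is 1.96 × √(2 × 0.25/60) = 17.9 points. For 33.25% against 26.6% the standard error is √(0.3325 × 0.6675/60 + 0.266 × 0.734/60) = 0.083. The half-width is then about 16 points and two-sided power about 12%. Neither form of the endpoint could detect an error of this size.

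**The opposite error.** AVS may also wrongly lateralise a bilateral patient. Assume 60% bilateral (Background), 20% of them additionally lateralised in one arm, remission on MRAs 0.5, and success after the wrong operation 0.2. Then 0.60 × 0.20 = 0.12 of the arm is affected.
- Pooled endpoint: 0.12 × (0.5 − 0.2) = 3.6 points lower in the worse arm.
- Success after adrenalectomy over all randomised: 0.12 × 0.2 = 2.4 points higher in the worse arm.

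So neither measure alone catches both errors.

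**The case against.** Comparing the outcome of AVS-guided management in everyone randomised is a legitimate question. It respects intention to treat and avoids selecting on treatment route, which is decided after randomisation. This stands, and it is why the pooled comparison should stay. It does not make the pooled rate a measure of subtyping.

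Fig. 3, which holds the detailed criteria, is not shown and might adapt them for medicated patients. A condensed article may also leave follow-up sampling conditions to the full protocol. Both are possible. However, the caption reads only as the PASO table, and the text describes the criteria as surgical while recording both routes in it.

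Three stronger readings are tempting, and the documents do not support them.
- *The endpoint is invalid for about 60% of participants.* The 60% is a background figure for bilateral hyperplasia in P.A. generally. Participants here want AVS, those who refuse or are at high risk of adrenal surgery are excluded, and L.I. ≥ 2 decides the route. The medicated share is unknown.
- *Wrong subtyping is masked.* The article says only that MRAs may affect renin and aldosterone. It gives no direction for ARR and no remission rate. In the illustration the error still moves the pooled rate by 1.8–4.6 points. It can be masked in part.
- *Success after adrenalectomy over all randomised would be a better primary endpoint, 1.5 to 3.8 times as sensitive.* That ratio (6.65/4.55 to 6.65/1.75) holds for missed unilateral patients only. With false lateralisation that endpoint can favour the worse arm, as shown above.

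**Conclusion.** The concern holds as a limit on what the primary endpoint can show. Criteria that the article ties to adrenalectomy in unilateral disease are pooled over operated and medicated patients. The resulting rate does not have one meaning, and a true difference in subtyping can be diluted. In the illustration, a 6.7-point effect shrinks to 1.8–4.6 points. This rests on the assumed miss rate, surgical remission rate and MRA remission rate, and on a background share of unilateral disease. The conclusion also assumes that the unseen Fig. 3 contains no separate criterion for medicated patients. The documents do not justify replacing the primary endpoint. They justify not resting a claim of unaffected subtyping on equal pooled remission rates, and reporting measures closer to subtyping beside them.

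**What to change.** Keep the all-randomised comparison of biochemical remission, and state that equality of the pooled rate alone will not be taken as evidence that subtyping is unaffected. Then, by arm:

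1. Report the lateralisation rate (L.I. ≥ 2) over all randomised, with a 95% confidence interval for the difference, as a key secondary outcome.
2. Report PASO complete biochemical success after AVS-guided adrenalectomy over all randomised, with a 95% confidence interval. Show it together with PASO results among operated patients, so that false lateralisation is visible as well as missed unilateral disease.
3. Report potassium and orthostatic ARR in medicated patients separately, labelled as on-treatment values and not as PASO remission.
4. Treat PASO clinical remission in the same way.

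If Fig. 3 or the full protocol already defines remission for medicated patients, say so in the outcome text.

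Cost: an amendment to the secondary outcomes and a registry update, made before any results by arm are seen, and a few more analyses. No new data are needed, since L.I., potassium and ARR are already collected. Comparisons within operated or within medicated patients are descriptive only, because the route is decided after randomisation. Power stays limited at 60 per arm, and these additions do not cure that.

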**Fig. 3 Fig3:**
[figure not shown]
PASO table

#### Secondary outcome

Rate of clinical remission

Biochemical outcome evaluation in 3 and 6 months after AVS: blood pressure, types, and dose of antihypertensive drugs. All these data will be recorded in the PASO table. The detailed criteria of complete, partial, and absent clinical remission are shown in Fig. 3.2.Successful catheterization rate

Intraoperative bilateral S.I. value was used to determine whether the blood collection cannula was successful. In the surgery without corticotropin, S.I. ≥ 2 was used as the standard for successful blood collection and L.I. ≥ 2 was used for judging the dominant side aldosterone secretion. S.I., selective index; L.I., lateralization index; Dom, dominant side; IVC, inferior vena cava; Nondom, nondominant side; PAC, plasma aldosterone concentration; PCC, plasma cortisol concentration. S.I. = PCC_side_/PCC_IVC_; L.I. = PAC_Dom_/PCC_Dom_:PAC_Nondom_/PCC_Nondom_.3.Adverse events

Record the occurrence of adverse events, including adrenal venous hemorrhage and related adrenal insufficiency, hypertensive urgencies, anaphylactic shock, venous thrombosis, pulmonary embolism, etc.

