Raising the accuracy of diagnosis and subtyping is extremely important for P.A. patients. Screening of P.A. is based on the aldosterone to renin ratio (ARR), and people with abnormally elevated ARR should be screened by further oral salt loading or captopril confirmatory tests [13]. P.A. subtyping test is also an essential, although difficult and challenging, step [13]. Adrenal venous sampling (AVS) was now regarded as the gold standard for P.A. subtyping but only performed in limited centers [12, 14]. Our team was experienced in this technique. Recently, we have developed a computed tomography image fusion, coaxial guidewire technique, and fast intraprocedural cortisol testing (CCF) technique, which significantly increased the success rate of AVS to 98% and shortened the whole procedure time [15]. Moreover, we are still committed to exploring a more optimized AVS procedure.

AVS outcome was interpreted by comparing aldosterone levels in the adrenal venal of the dominant and nondominant side, which could be affected by the position change [16]. Before AVS without corticotropin injection, patients were suggested to keep a supine position to avoid aldosterone fluctuation [13, 17]. However, the length of supine time before AVS had no established standard, although authoritative guidelines recommend recumbency times ranging from 1 h to overnight [13, 17]. In previous work, we chose 1–2 h of supine time as the guideline suggested [17]. We observed many problems were caused by excessive supine time, such as patient’s urinary retention and anxiety, while reduced supine time was found to be more friendly for these patients.

The cortisol level of patients is also an important factor affecting the selective index (S.I.) during AVS. A cohort study showed that at least 15 min of rest before blood sampling was enough to minimize the stress effect and guarantee a satisfactory outcome [18]. Thus, we speculate that 15-min supine time is enough to minimize the fluctuation of aldosterone and cortisol fluctuation caused by position change and preoperative stress.

However, evidence of the most optimal supine time before AVS still lacks, which could simultaneously improve patient satisfaction and compromise the success rate. We expect that the shortened supine time will improve patient experience and ensure the success rate at the same time.

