### Sample size

The sample size calculation was performed using the PASS15 software, version 15.0.5, with reference to a prior randomized controlled trial that reported the value of targeting CXCR4 with 68Ga-Pentixafor PET/CT for subtyping P.A., which enrolled 120 cases [19]. According to this study protocol, a sample size of 60 participants in each group was calculated to sufficiently detect the target effect size (0.5) with a type I error of 5% (*α* = 0.05) and 90% power (*β* = 0.10) by the PASS15.0 software. Allowing for a 20% loss to follow-up, this study was designed to include 120 cases.

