### Recruitment

Some efforts will be made to ensure enough participant enrollment in this study: more than 200 patients were eventually diagnosed as P.A. in our centers, and 100–120 AVS surgeries were performed each year in our centers with a success rate higher than 95%. Therefore, we think we need 1–1.5 years to enroll enough cases. Besides, we would implement a poster recruitment strategy in our hospital and on the Internet, which contains detailed information about this trial’s objective, contact method, and attention matters. Further, a specific member will help interested participants to complete registration for the trial.

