### Assignment of interventions: allocation

#### Allocation-sequence generation

Random numbers within the range of 1 to 120 will be generated by an independent statistician using the SPSS V25.0 software. The allocation of participants will be determined based on the parity of the generated random numbers. Participants with an odd random number were assigned to the 15-min group, and participants with an even random number were assigned to the 2-h group.

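### The only AVS-level efficacy outcome is a yes/no S.I. ≥ 2 rate near its ceiling, and the S.I. and L.I. values that carry the trial's premise are not named as outcomes

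*Protocol article*

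**What the plan says.** The Objectives section of the protocol article sets out to compare 15 minutes with 2 hours supine for the efficacy of AVS. Trial design gives the hypothesis that the shorter time leaves subtyping performance unchanged. The reason offered is that 15 minutes is enough to settle cortisol and aldosterone.

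The primary outcome is biochemical remission at 3 and 6 months. The secondary outcomes are clinical remission, successful catheterization and adverse events. Catheterization success is judged on the S.I. of both sides: "In the surgery without corticotropin, S.I. ≥ 2 was used as the standard for successful blood collection". L.I. appears only as a cut-off of 2 for the dominant side. Formulas are given for both indices, but neither value is listed as an outcome.

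Recruitment says that 100–120 AVS procedures are "performed each year in our centers with a success rate higher than 95" per cent. Background says that the team's technique "significantly increased the success rate of AVS to 98" per cent, and that previous work used 1–2 h supine. For the test, Statistical analysis says: "Categorical variables will be expressed as frequency (%), and the chi-square test will be used to compare the differences between the two groups". The same section gives t or Mann–Whitney tests for continuous variables in general and promises 95% confidence intervals for effect estimates.

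**The concern.** S.I. is built from cortisol, and L.I. from aldosterone and cortisol. They are the quantities through which supine time would act. Remission at 3 and 6 months comes after surgery or drug treatment and is further from the intervention. Catheterization success is therefore the efficacy outcome nearest to the question, and it is reduced to a yes/no that the centres already achieve almost always.

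A yes/no outcome near 100% has few failures to compare, so moderate harm from the shorter time would usually go undetected. The investigators expect no effect and state no margin. A p value above 0.05 could then be read as support for 15 minutes when the trial had little chance of showing otherwise.

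**Working it through.** **Number per arm.** The article gives no power figure for catheterization, so the headcount comes from Sample size: "a sample size of 60 participants in each group was calculated to sufficiently detect the target effect size (0.5". Alpha is set at 0.05 and power at 90%. That figure does not reproduce as a two-sided standardised mean difference: n = 2(1.960 + 1.282)²/0.5² = 84.06, so 85 per arm. This is a separate matter. Here 60 is used only as the number randomised per arm. It is also the best case, because S.I. is measured at AVS, before any follow-up loss. If the full 20% loss applied, 60 × 0.8 = 48 per arm would remain.

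**Expected failures.** At 95% success, 60 × 0.05 = 3.0 per arm; at 98%, 60 × 0.02 = 1.2.

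**Power of the dichotomy** (two-sided 0.05; sidedness is not stated, so this is an assumption). Normal approximation, with p̄ the mean of the two rates:

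power = Φ{ [|p₁ − p₂| − 1.96 √(2p̄(1 − p̄)/n)] / √([p₁(1 − p₁) + p₂(1 − p₂)]/n) }

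For 95% against 90%: p̄ = 0.925, 1.96 × 0.0481 = 0.0943, denominator 0.0479. Then Φ[(0.05 − 0.0943)/0.0479] = Φ(−0.92) = 0.18. Exact enumeration of two binomials with the uncorrected chi-square test gives:

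| 2-h arm | 15-min arm | Power, 60 per arm |
|---|---|---|
| 97% | 93% | 15% |
| 95% | 90% | 17% |
| 98% | 93% | 24% |
| 97% | 90% | 34% |
| 95% | 85% | 46% |
| 98% | 88% | 61% |
| 98% | 85% | 78% |
| 95% | 75% | 90% |
| 98% | 80% | 94% |

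By the normal approximation, 90% power is reached at 95% against 73.9% (a 21.1-point fall) or 98% against 79.6% (18.4 points). For a 5-point fall, 90% power would need 582 per arm from 95%, or 360 from 98%.

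**Type I error.** Enumeration with equal true rates gives 0.046 at 95%, 0.035 at 97% and 0.019 at 98%. The test is conservative, not inflated.

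**What the interval shows.** Take 3 failures of 60 on 2 h and 6 of 60 on 15 min. Chi-square = (0.05/0.0481)² = 1.08, p = 0.30. The Wilson score limits are 1.7–13.7% and 4.7–20.1%. Combined by Newcombe's method, the increase in failures is 5.0 points. Its lower limit is 5.0 − √(5.3² + 8.7²) = −5.2 and its upper limit is 5.0 + √(10.1² + 3.3²) = 15.7. The p value suggests nothing happened, while the interval still allows a loss of about 16 points.

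**Information lost by dichotomising.** Assume log S.I. is normal with common SD, and treat success as one index crossing the cut-off (a simplification, since success is bilateral). A shift of 0.5 SD compared as a continuous value has power Φ(0.5 × √(60/2) − 1.96) = Φ(0.78) = 78%. The same shift at the cut-off moves 95% to Φ(1.645 − 0.5) = 87.4%, or 98% to Φ(2.054 − 0.5) = 94.0%. Exact chi-square power is then 32% or 18%.

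**The case against.** The strongest reply is that a high success rate suits a question about no difference, because proportions near 1 give narrow intervals. With an assumed 10-point margin, one-sided 0.025 and equal true rates, 60 per arm gives 71% power at 95% success and 97.5% at 98%. This stands, and it is why the remedy rests on the interval. It does not rescue a chi-square p value read without a margin, and at a 5-point margin the same figures are 24% and 50%.

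A reader might infer that the outcome cannot show an effect at all. The documents do not support that. The 95–98% is historical, previous work used 1–2 h supine, and no rate is given for 15 minutes. A large fall would be found, as the table shows.

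A reader might also infer that expected counts below 5 make the chi-square test invalid and that Fisher's test is the cure. Its true size stays below 5%, and Fisher's test lowers power further, from 17% to 9% for 95% against 90%.

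It is also fair to say that the generic rule for continuous variables could cover S.I. and L.I., and that an analysis plan not shown may do so. So one cannot say the values will go uncompared, only that the protocol's outcome list does not name them. Confidence intervals are already promised. Finally, this is a secondary outcome, and Recruitment does not say that its success rate uses the S.I. ≥ 2 definition.

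**Conclusion.** The point holds as an inexpensive improvement to a secondary outcome. It is not a fault that invalidates the trial. The one AVS-level efficacy outcome is sensitive only to large falls: about 15–35% power for falls of 4–7 points, and 90% power only at about 18–21 points. A non-significant result would be weak evidence that shortening supine time is harmless. The values that bear directly on the hormonal premise are measured but not named as outcomes.

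The figures assume 60 per arm with AVS results, a two-sided 5% test and a 2-h success rate of 95–98%. The continuous comparison also assumes a normal log S.I. The documents give no SD for log S.I. or log L.I., so the 0.5 SD shift shows relative efficiency, not an expected effect.

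One further inference should be left aside: that rapid cortisol testing lets low samples be repeated until both arms succeed. The sampling procedure describes quick measurement but no resampling, so nothing here rests on it.

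**What to change.** Keep the catheterization success rate. State that it will be interpreted through the between-arm difference with a score-based 95% confidence interval, and that p > 0.05 will not be taken as evidence of no effect.

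Name as secondary AVS-level outcomes the between-arm ratio of geometric means, with 95% confidence interval, for S.I. on the right, S.I. on the left and L.I., in all randomised patients who were sampled, analysed as allocated.

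The cost is a few lines of outcome and analysis wording. The hormone values are already obtained, so no sample or visit is added. The downside is three more secondary comparisons, which should be labelled supportive.
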